### In vitro assays

#### Blood samples

Blood samples will be collected from all patients at baseline, T1, and T2. Heparinized tubes will be immediately centrifuged at 1500 × *g* for 5 min at 4 °C for separation of plasma and cells. These samples will be centrifuged within 6 h of collection. Plasma will be stored at − 80 °C until the time of analysis. The cell pellet will be used for monocyte and neutrophil isolation and evaluation, while plasma will be used later (after perioperative monitoring) for quantification of C-reactive protein (CRP), procalcitonin (PCT), IL-6, IL-10, and TNF-α levels.

#### Adipose tissue fragments

Adipose tissue fragments will be subjected to enzymatic digestion with 1 mg/mL collagenase IA (Sigma Chemical Co., St. Louis, USA) for 30 min at 37 °C. The remaining tissue will be filtered through a 100-mm pore nylon mesh, and proteolysis will be interrupted with high-glucose Dulbecco’s modified Eagle’s medium (DMEM, Gibco, Invitrogen, NY, USA) with 20% fetal bovine serum (FBS) (Hyclone Laboratories Inc., UT, USA) and 1% penicillin and streptomycin solution (Gibco, Invitrogen, NY, USA). The cells will be centrifuged and washed twice with 0.01 mM phosphate-buffered saline (PBS), and will then be prepared for magnetic selection.

Total leukocytes obtained from blood and adipose tissue will be analyzed by diluting the samples in Türk’s liquid (1:10) and counting cells in a Neubauer chamber under a light microscope (BX51, Olympus, Tokyo, Japan). Slides will be stained for the differential cell count using the May- Grünwald-Giemsa method and visualized with an oil- immersion objective under the same microscope. Monocytes and neutrophils will be isolated by the magnetic sorting technique (Invitrogen, CA, USA) through incubation with biotin-associated anti-CD11b and anti-CD11c antibodies, respectively, followed by incorporation with biotin- coated iron beads and exposure to a magnetic field for 10 min.

Total messenger RNA (mRNA) will be extracted from cells using the Reliaprep RNA Tissue Miniprep System RNA extraction kit (Promega, Madison, WI, USA), following the manufacturer’s recommendations. After extraction, the precipitated RNA will be solubilized in 20 μL of diethylpyrocarbonate (DEPC)-treated water. The total RNA concentration will be measured by spectrophotometry in a Nanodrop ND-1000 system. The integrity of the samples will be verified by 1% agarose gel electrophoresis containing 0.5 μg/mL of ethidium bromide. First-strand complementary DNA (cDNA) will be obtained from total RNA using the High Capacity cDNA Reverse Transcription kit (Invitrogen, CA, USA). Relative mRNA levels will be measured using BRYT Green (Promega, Fitchburg, WI, USA) using a Mastercycler® ep Realplex PCR system (Eppendorf, Hamburg, Germany). All experiments will be performed in triplicates. Growth factors and inflammatory mediators will be analyzed by real-time RT-PCR. The relative level of each gene will be normalized to the housekeeping gene acidic ribosomal phosphoprotein P0 (*36B4*) and expressed as fold change relative to each individual at initial conditions, using the 2^−ΔΔ^ cycle threshold (Ct) method, where ΔCt = Ct (target gene) − Ct (housekeeping gene). Neutrophil and macrophage gene expression in vitro will be analyzed by an investigator blinded to group assignment.

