#### Secondary

The secondary endpoints are (1) the differences in levels of other proinflammmatory and anti-inflammatory mediators in blood, subcutaneous tissue, and visceral adipose tissue, namely (a) inflammatory mediators associated with neutrophils: metalloprotease (MMP)-2 [36–38], MMP-9 [36], CXCR2 [39], IL-12 [40], CCL3 (macrophage inflammatory protein (MIP)-1α) [41–44], CCL2 (MCP1) [44], IL-1β [45], TNF-α [46], NRF2 [47, 48], (b) mediators associated with macrophages: proinflammatory (IL-1β, CD40 [49], CD80 [50]), M1 phenotype markers (TNF-α, IL-6 [51–53], iNOS [54–56]), anti-inflammatory (IL-1 receptor antagonist (IL-1RA) [57–59], NrF2), M2 phenotype markers (CD163 [60, 61], CD206 [62], arginase [63, 64], IL-10 [65], transforming growth factor (TGF)-β1 [66–68]), and (c) mediators associated with cell death pathways (BCL2-associated X (Bax), bcl2 [69, 70], caspases 3 and 9 [71–73]); (2) intraoperative complications: (a) hypoxemia (PaO_2_/FiO_2_ ratio < 300), (b) hypotension (systolic blood pressure < 90 mmHg), (c) bradycardia (heart rate < 50 bpm), (d) unexpected need for intensive care unit (ICU) admission or readmission, (e) length of hospital stay, (f) number of days at home in the first month after surgery, and (g) postoperative complications: pulmonary infection (defined as new or progressive radiographic infiltrate and at least two of the following criteria - antibiotic treatment, axillary temperature > 38 °C, leukopenia (WBC < 4000 cells/mm^3^) or leukocytosis (WBC > 12,000 cells/mm^3^), and/or purulent secretions); sepsis (defined as suspicion or certainty of infection and an acute increase ≥ 2 points in the Sequential Organ Failure Assessment Score (SOFA) in response to an infection, representing organ dysfunction); septic shock (defined as sepsis plus need for vasopressor to maintain mean blood pressure > 65 mmHg plus lactate > 2 mmol/L [18 mg/dL] after adequate volume resuscitation [74–76]); extrapulmonary infection (of the operative wound or any other infection); coma (Glasgow Coma Scale < 8 in the absence of therapeutic sedation); acute myocardial infarction (according to the universal definition thereof [77]); acute kidney failure (according to the risk, injury, failure, loss, end-stage renal failure (RIFLE) criteria classification system [78]); DIC (according to the International System for the Evaluation of Thrombosis and Hemostasis for DIC [79]); GIF (defined according to the GIF score [80]); acute liver failure (defined as a ratio of total bilirubin on the 5th postoperative day to the 1st postoperative day > 1.7 plus a ratio of international normalized ratio (INR) on the 5th postoperative day to the 1st postoperative day > 1.0 or presence of hepatic encephalopathy and INR > 1.5) [81, 82].

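### As written, the magnetic sort (anti-CD11b for monocytes, anti-CD11c for neutrophils, biotin on both antibody and bead) would not yield the named cell types, so the cell-specific secondary gene-expression readouts could not be cleanly attributed

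*Protocol article*

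**What the plan says.** All references are to the protocol article.

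- **Starting material.** Under Blood samples, after centrifugation: "The cell pellet will be used for monocyte and neutrophil isolation and evaluation". Under Adipose tissue fragments, fat is digested, filtered, washed and prepared for magnetic selection.
- **Sort.** Under Adipose tissue fragments, for leukocytes from blood and fat: "Monocytes and neutrophils will be isolated by the magnetic sorting technique (Invitrogen, CA, USA) through incubation with biotin-associated anti-CD11b and anti-CD11c antibodies, respectively". The word order assigns CD11b to monocytes and CD11c to neutrophils. The beads named next carry biotin too: "coated iron beads and exposure to a magnetic field for 10 min".
- **Microscopy.** "Slides will be stained for the differential cell count using the May- Grünwald-Giemsa method". This comes before the sorting sentence and concerns total leukocytes, not the sorted fractions.
- **Readout.** The same section extracts mRNA from the cells, normalizes expression to a housekeeping gene and reports it as fold change from each patient's initial state. It adds: "Neutrophil and macrophage gene expression in vitro will be analyzed by an investigator blinded to group assignment".
- **Endpoints.** Under Secondary, item (1) groups the mediators by cell type, with (a) "inflammatory mediators associated with neutrophils" and (b) "mediators associated with macrophages: proinflammatory", followed by the M1 and M2 phenotype markers.

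**The concern.** A readout labelled as neutrophil or macrophage expression means what its label says only if the sorted fraction is mostly that cell. The sorting sentence has two defects.

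First, the markers do not separate the two cell types. CD11b is found on both, and CD11c points towards monocytes, macrophages and dendritic cells and away from neutrophils. Second, antibody and bead both carry biotin, and no linking reagent is named.

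At stake is the interpretation of the cell-specific results. RT-PCR on a mixed fraction returns an average over whatever cells are present. A difference between anesthetics could then reflect a change in expression, a change in cell mix, or both. This bears on the article's stated aim of describing monocyte/macrophage polarization.

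**Working it through.** The article states no figure that bears on this point, so the check is textual, with one line of algebra.

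**1. Does the stated pairing isolate the named cells?** The marker facts below are general immunology. The article does not state them, and nothing in it contradicts them.

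| Fraction named in the article | Stated marker | Cells expected to carry it |
|---|---|---|
| Monocytes | CD11b | monocytes/macrophages and neutrophils |
| Neutrophils | CD11c | mainly monocytes, macrophages, dendritic cells |

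The first fraction would be mixed and the second mainly the wrong cells.

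**2. Does any other step rescue the separation?** The article describes no second lineage marker, gradient, depletion, order of sorting or purity check of the fractions. The blood sort is described as starting from the pellet, which contains both cell types.

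**3. Would reversing the pairing be enough?** With CD11c for monocytes, that fraction becomes plausible. With CD11b for neutrophils, the fraction still includes monocytes unless CD11c-positive cells are removed first. No such order is given.

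**4. The capture step.** Biotin-linked antibody plus biotin-coated bead leaves no binding partner, so read literally nothing is captured. If the laboratory in fact uses a streptavidin-type bead, capture works and the marker problem in step 1 applies. These are alternatives and should not be added together, but under either one the sentence needs correction.

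**5. What a mixed fraction does to the comparison.** Let p be the neutrophil share of the measured signal, and N and M the normalized expression in neutrophils and in monocytes/macrophages. The fraction shows

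X = p·N + (1 − p)·M.

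- If N and M are the same in both arms but the mix differs, X(sevoflurane) − X(propofol) = (p_S − p_P)·(N − M). This is non-zero although neither cell type has changed its expression.
- If the mix is the same in both arms and only M differs, the observed difference is (1 − p)·(M_S − M_P). It is diluted and not assignable to one cell type.
- A shift in p common to both arms does not by itself create a difference between arms. Only a differential shift does.

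**6. Which results depend on the sort?** Those that depend on it are the cell-specific gene-expression readouts behind secondary items (1)(a) and (1)(b). Plasma IL-6, the plasma measures of C-reactive protein, procalcitonin, IL-10 and TNF-α, the sample-size calculation and the clinical endpoints do not.

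**The case against.** **This may be a wording slip in a condensed article.** Bench steps are usually left to a laboratory procedure that is not shown here. The word order may be reversed, or a sequential sort may be used. That is possible, and it is why the request is to correct the sentence. It does not remove the point: the article states the reagents and their pairing, and the stated method does not work. This is a different matter from leaving a detail out.

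**The marker premise is not in the document.** That is true for CD11b and CD11c, which rest on general knowledge of cell-surface markers. The bead chemistry shows a defect in the text itself.

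**Not every secondary mediator depends on the sort.** This stands. The Secondary section names mediators in blood and in both fat depots. Several, such as TNF-α, IL-1β and NRF2, appear in both cell lists, and TNF-α and IL-10 are also measured in plasma.

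**Stronger readings that a reader might infer:**

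- *That the blood monocyte fraction would be almost all neutrophils.* Assuming 40–75% neutrophils and 2–10% monocytes among leukocytes, the neutrophil share runs from 40/(40 + 10) = 80% to 75/(75 + 2) = 97%. The article gives no differential count. The range assumes equal capture, counts only these two cell types and says nothing about fat. It is not a finding.
- *That the M1/M2 hypothesis could not be answered.* The Abstract places that hypothesis in adipose tissue, and the Background says macrophages predominate among the immune cells there. A CD11b selection from fat would be expected to yield mainly macrophages. Table 2 describes CD163 and CD206 as macrophage markers, so they keep some meaning in an imperfect fraction. Nor does the article describe repeated fat sampling, so the argument about a shift in cell mix during surgery applies to blood.

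**Conclusion.** The concern holds in limited form. As stated, the sort would not yield the named cell types, and no described step compensates. The cell-specific readouts could not be cleanly attributed to neutrophils or to monocytes/macrophages. In blood, a between-arm difference in cell composition could pass for a difference in expression.

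No numerical size can be given, because the article reports neither a differential count nor a purity figure. The reach is confined to the cell-specific secondary gene-expression results of a trial that calls itself a pilot. The conclusion assumes that the laboratory follows the sentence as written and that the usual expression of CD11b and CD11c applies. An unshown procedure may already differ, in which case the published sentence is what needs correcting. The point should be fixed, but it does not threaten the primary analysis.

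**What to change.** Before sampling, correct the sorting sentence so that:

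1. Each cell type is selected with a lineage marker that separates it, for example CD14 for monocytes/macrophages and CD66b or CD15 for neutrophils. The marker should not itself be an M1/M2 endpoint. CD206 is unsuitable because sorting on it would enrich for the M2-like cells being measured.
2. A capture step that binds the biotin-linked antibody is named, such as streptavidin-coated beads.
3. The purity of every sorted fraction is recorded, using the May-Grünwald-Giemsa stain already planned for total leukocytes.

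Report purity by arm and use it in a sensitivity analysis of the cell-specific readouts. Do not drop low-purity samples: purity is observed after randomization, so exclusion would create missing data that could differ between arms. For the same reason, a purity-adjusted result should support the unadjusted comparison and not replace it.

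The cost is a small change to the laboratory protocol and extra slide reading. If all 48 patients give three blood samples and one sample from each of two fat depots, and both fractions of each are read once, that is 48 × (3 + 2) × 2 = 480 readings. If the laboratory already uses a sound sort, only the text correction and the purity record are needed. The timing matters because cells cannot be re-sorted once their RNA has been extracted.

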**Discussion:**

To our knowledge, this is the first randomized clinical trial designed to compare the effects of two different anesthetics on immunomodulation in obese patients undergoing laparoscopic bariatric surgery. Our hypothesis is that anesthesia with sevoflurane will result in a weaker proinflammatory response compared to anesthesia with propofol, with lower circulating levels of IL-6 and other proinflammatory mediators, and increased macrophage differentiation into the M2 phenotype in adipose tissue.

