### Samples

Blood (15 mL) will be collected in heparinized tubes prior to induction of anesthesia (baseline), immediately after anesthetic induction (T1), and before extubation (T2).

Two small fragments of subcutaneous adipose tissue and visceral adipose tissue will also be sampled. Each fragment will measure 2 × 2 × 2 cm after excess blood vessels and connective tissue have been removed with the aid of a scalpel, and will be obtained from surgical specimens that would be discarded immediately following gastroplasty.

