
## Statistical analysis

Positive modulation of the IL-6 receptor and IL-6 expression in adipose tissue is known to occur in obesity [51, 83]. A convenience sample of 48 patients has been chosen on the basis of a study in which plasma IL-6 levels were compared before and after anesthesia in patients undergoing thoracic surgery with one-lung ventilation [84]. The sample size was calculated using G*Power 3.1.9.2 software (University of Dusseldorf, Germany), taking into account an effect size of 1.33, a two-sided test, and a ratio of 1. A sample size of 10 patients in each group will provide adequate power (80%), assuming α = 0.05, to detect at least an effect size of 33% difference in IL-6 levels in plasma samples collected immediately after induction of anesthesia and before extubation in obese patients anesthetized with sevoflurane or propofol (*p* = 0.05). Considering possible losses and to obtain even more significant results, we chose to increase the sample to 24 patients per group. Data will be tested for normality and variability. Comparison of the parameters of interest between participants in the sevoflurane and propofol groups will be performed by Student’s *t* test or the Wilcoxon test, as appropriate. Statistical significance will be accepted at *p* < 0.05. All analyses will be undertaken by an independent statistician, who will be blinded to group allocation.

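### The own-baseline fold change prescribed for gene expression has no reference sample in adipose tissue, so the fat outcomes need a between-arm ΔCt comparison

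*Protocol article*

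**What the plan says.** Under In vitro assays, Adipose tissue fragments, each gene is first referred to the reference gene 36B4, "where ΔCt = Ct (target gene) − Ct (housekeeping gene"). It is then "expressed as fold change relative to each individual at initial conditions" by the 2^-ΔΔCt method. No exception is made for any tissue, and the phrase about initial conditions is not defined.

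The sampling differs by tissue:

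- Blood: "Blood samples will be collected from all patients at baseline, T1, and T2". The baseline draw precedes induction.
- Fat (Samples): "Two small fragments of subcutaneous adipose tissue and visceral adipose tissue will also be sampled". The fragments "will be obtained from surgical specimens that would be discarded immediately following gastroplasty". No time points are listed for fat.

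The fat results matter to the plan. The first secondary endpoint covers "mediators in blood, subcutaneous tissue, and visceral adipose tissue", and the hypothesis in the abstract's Discussion includes "increased macrophage differentiation into the M2 phenotype in adipose tissue". The Statistical analysis section tests between arms: "Comparison of the parameters of interest between participants in the sevoflurane and propofol groups will be performed by Student’s" t test or the Wilcoxon test.

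**The concern.** A fold change against the patient's own starting value needs two samples of the same tissue, one taken before exposure. Blood has the earlier sample and fat does not. The rule appears under the heading for adipose tissue, in text that deals with cells from both blood and fat, so it cannot simply be read as a rule for blood.

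Two things are at stake. First, someone will have to choose a reference for the fat data that the plan does not name. The candidates are not all equivalent, and the choice is best made before any data are seen. Second, a result labelled as a fold change from initial conditions would be read as a change under anesthesia, which one intraoperative sample cannot show.

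**Working it through.** **The plan's own figure.** The only computed figure is 10 patients per group for plasma IL-6 (effect size 1.33, two-sided α = 0.05, 80% power). A two-sample t test with the noncentral t distribution gives 9.93, rounded up to 10, with 80.3% power at 10. The figure reproduces, and the present point does not depend on it.

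**The formula.** For patient i and one gene:

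- ΔCt_i = Ct_i(target) − Ct_i(36B4), which needs one sample.
- ΔΔCt_i = ΔCt_i(sample) − ΔCt_i(initial), which needs two.
- Fold change_i = 2^-ΔΔCt_i.

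**The samples described.**

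| Tissue | Before induction | Later | ΔCt | Own-baseline ΔΔCt |
|---|---|---|---|---|
| Blood cells | baseline | T1, T2 | yes | yes |
| Subcutaneous fat | none described | surgical specimen | yes | no reference |
| Visceral fat | none described | surgical specimen | yes | no reference |

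**What each possible reference would do for fat.**

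1. *The fat sample itself.* ΔΔCt_i = ΔCt_i − ΔCt_i = 0, so the fold change is 2^0 = 1 for every patient in both arms. No comparison is left.
2. *One common value c for all patients.* The arm difference is mean(ΔCt − c) in one arm minus mean(ΔCt − c) in the other, so c cancels. In one simulated data set with 24 per arm, c = 0, 3 and 5.2 all gave a difference of 0.295 in ΔCt and a ratio of 2^0.295 = 1.227.
3. *The patient's own baseline blood cells.* Each value is then a contrast between two tissues. That blood is drawn before either agent is given, so under randomization its expected ΔCt is the same in both arms, and the arm difference on the log2 scale still estimates the anesthetic effect in fat. What changes is precision. If fat and blood ΔCt have equal SD σ and correlation ρ (both assumptions), the variance is 2(1 − ρ)σ²: twice that of fat alone at ρ = 0, 1.4 times at 0.3, equal at 0.5, and 0.6 times at 0.7. Noise is added whenever ρ is below 0.5.
4. *No reference: ΔCt compared between arms.* This is computable from one sample per patient. At 24 per arm, 80% power and two-sided α = 0.05, the detectable difference is 0.826, or about 0.83 SD of ΔCt. With own baseline blood as reference and ρ = 0, it would be 0.826 × √2 = 1.17 SD.

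Options 2 and 4 give the same arm contrast, option 3 gives a different estimate of the same quantity, and option 1 gives nothing.

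**The case against.** The strongest reply is that this is a laboratory detail which a condensed article may leave to the full protocol or a laboratory manual. Single sampling of fat is also inferred: the Samples section does not say it in words, and the SPIRIT schedule (Fig. 2) is not shown. The inference is sound, though, on the point that matters. Tissue discarded after gastroplasty cannot supply a sample from before anesthesia. And the article does not leave the scale open. It states one, without exception, that does not fit the fat samples it describes.

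The other side does defeat several stronger readings that a reader might infer:

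- *The adipose outcomes cannot be computed.* Not supported. The endpoint is a difference between arms, and the ΔCt that the article defines needs no baseline. Adipose leukocyte and differential counts do not use this scale at all.
- *A blood reference would show only a tissue difference.* Not supported, as the third option above shows. It affects precision and does not bias the randomized contrast.
- *The choice of reference could steer the result.* Largely not. A common reference cancels, gene expression is assessed by an investigator blinded to group, and the statistician is blinded too.
- *Skewed fold changes invalidate the test.* The plan checks normality and allows the Wilcoxon test. A rank test of the arms gives the same answer on 2^-ΔΔCt as on ΔΔCt, because one is a monotone function of the other.
- *Two thirds of all marker comparisons are lost.* That fraction only restates that two of the three compartments are fat. The secondary endpoint lists 9 + 13 + 4 = 26 entries, but IL-1β, TNF-α and Nrf2 appear twice, leaving 23 distinct markers. The text does not say that all of them are PCR outcomes in every compartment.

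**Conclusion.** The plan is wrong as written, within narrow limits. The prescribed own-baseline fold change is undefined for subcutaneous and visceral fat, including the M2 markers measured there by RT-PCR. The Samples section and the gene-expression paragraph need to be reconciled. What is unavailable in fat is the within-patient change and any adjustment for a fat baseline. A valid randomized comparison from the single sample remains.

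Severity is moderate. The affected results are secondary endpoints in a trial that calls itself a pilot, and plasma IL-6, the sample size and the randomization are untouched. The conclusion assumes that no pre-anesthesia fat sample appears in the schedule that is not shown. The 0.83 SD also assumes evaluable tissue from all 24 patients per arm.

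**What to change.** 1. Limit the own-baseline 2^-ΔΔCt fold change to blood cells, and define the initial condition as the pre-induction sample.
2. For each fat depot separately, compare ΔCt (target minus 36B4) between arms. Report 2^-(mean ΔCt with sevoflurane − mean ΔCt with propofol) as the fold difference, with a 95% CI obtained by back-transforming the limits of the ΔCt difference.
3. State that the fat results are single-time comparisons between arms and not changes from baseline.
4. For blood, analyze ΔCt at T2 adjusted for baseline ΔCt. This keeps both tissues on the same log2 scale and uses the baseline that blood has. It is an improvement to the analysis and does not repair a contradiction.

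The cost is analysis wording only, with the same patients, samples and assays. It should be settled before the expression data are examined.
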